### Trial setting

2.3

This nationwide, multi-centre study will be conducted across Poland. Participants will be recruited from public antenatal clinics and outpatient departments, childbirth education schools, and through online platforms such as social media and parenting forums. Private maternity centres are excluded from recruitment to minimise selection bias. This multi-channel strategy ensures broad geographic reach and sample diversity. Intervention sessions will be delivered either in person at a location convenient for the participant or remotely via secure video conferencing. The study will be coordinated by the research team at the Medical University of Gdańsk.

### Eligibility criteria

2.4

#### Inclusion criteria

2.4.1

Women will be eligible for inclusion if they meet all of the following criteria: are at least 18 years of age, have a singleton pregnancy, are between 24 and 30 weeks of gestation at the time of recruitment, are fluent in Polish, are not receiving care exclusively at a private maternity centre, and score ≥30 points on the PRAQ-R2. Following a review of PRAQ-R2 score distributions across international validation samples—in which mean total scores ranged from approximately 22 points (SD 6.7) in a German third-trimester sample (44) to a median of 27 points (IQR 22–32) in a Chinese sample (45) and in light of Polish normative data reporting a mean score of approximately 31 points (38), this threshold was adopted for this study. It was established in a Polish single-centre pilot study and was associated with longer labour stages and higher rates of instrumental or emergency caesarean delivery (38). It is acknowledged that this cut-off captures women with elevated but potentially sub-clinical anxiety; however, given the absence of a universally validated diagnostic threshold for the PRAQ-R2 and given that most international adaptations recommend using the scale as a continuous measure (25, 45), this pragmatic threshold reflects the best available evidence in the Polish perinatal context.

#### Exclusion criteria

2.4.2

Women will be excluded from the study if they meet any of the following criteria: absolute or strong medical indication for caesarean delivery (e.g., placenta praevia); multiple pregnancy; diagnosis of a severe psychiatric disorder (e.g., active psychosis, schizophrenia, bipolar disorder) that could interfere with informed consent or study participation; current pharmacological treatment for anxiety or depression, regardless of symptom severity, as concomitant psychotropic medication may confound the assessment of intervention effects; concurrent participation in another structured psychological intervention; or inability to commit to the study schedule.

#### Eligibility criteria for intervention deliverers

2.4.3

Midwives delivering the intervention must meet all of the following criteria: hold a Master’s degree in midwifery, maintain current professional registration, and have a minimum of 2 years of clinical experience in obstetric or antenatal care. A minimum of 2 years was considered sufficient given that the intervention is protocol-based, does not require advanced psychotherapeutic qualifications, and is supported by a structured training programme completed by all participating midwives prior to delivery, covering the theoretical framework, session structure, psychoeducational techniques, and fidelity requirements.

Four to five midwives will be trained prior to trial commencement. Training objectives include: understanding Peplau’s theoretical framework; delivering the six-session protocol; applying anxiety management techniques; completing session logs; and recognising referral criteria. Competence will be confirmed via an observed practice session assessed by the principal investigator before each midwife proceeds to trial delivery. As fidelity is assessed by a single supervisor, formal inter-rater reliability testing is not applicable; this is acknowledged as a limitation.

### Intervention and comparator

2.5

#### Control group

2.5.1

Women in the control group will receive standard antenatal care as is typical in Poland, comprising: antenatal education in accordance with the Polish Organizational Standard of Perinatal Care (46), covering pregnancy, childbirth, puerperium and social support; routine obstetric appointments and ultrasound examinations; and hospital care during and after childbirth provided by designated hospital staff. In addition, women in the control group will receive an informational booklet on preparing for childbirth, developed specifically for this trial by midwives from the research team. The booklet covers key topics including the physiology of labour and birth, pain management options, hospital admission procedures, postpartum care, and newborn care. It is designed to provide factual information without therapeutic or psychoeducational components, thereby serving as a minimal active control condition that addresses ethical concerns while maintaining a meaningful contrast with the intervention.

Although standard antenatal education in Poland covers some overlapping topics (e.g., childbirth physiology), it is delivered in a group format without individualised psychological assessment or anxiety-focused components. The intervention differs fundamentally in being individually tailored to each participant’s anxiety profile and grounded in a structured therapeutic framework. To monitor the integrity of the control condition, participants will be asked at each follow-up assessment to report the content and format of antenatal education received; this information will be recorded and included as a covariate in sensitivity analyses if meaningful variability is identified.

Potential contamination between groups is addressed in detail in the Concomitant Care section, including measures to minimise cross-group communication and a planned sensitivity analysis.

#### Intervention

2.5.2

Women in the intervention group will receive the same standard antenatal care and informational booklet as the control group, in addition to an individual psychoeducational programme led by a trained midwife. The intervention is advisory and educational in nature, with the aim of providing psychological support, reducing anxiety, and increasing the expectant mother’s sense of control and competence. It is based on communication skills, empathy, obstetric knowledge, and the application of simple psychoeducational and relaxation techniques. The intervention will be conducted between the 24th and 34th weeks of pregnancy in the form of individual sessions, which can take place in person or via secure video conferencing, depending on participant preference. The programme typically comprises four to six sessions of approximately 60 min each, held every one to 2 weeks. Women recruited toward the end of the eligible window (i.e., at 29–30 weeks of gestation) can complete the minimum required four sessions prior to the 34-week primary outcome assessment by attending one to two sessions per week, which is consistent with the standard frequency and does not represent an undue burden.

As described in the Introduction, the intervention is grounded in Peplau’s Theory of Interpersonal Relations (47, 48). This framework is particularly well-suited to PrA, which is strongly predicted by low perceived control and insufficient support from healthcare providers (49). Peplau’s four sequential phases map directly onto the intervention sessions: Orientation (Session 1), Identification (Sessions 2–3), Exploitation (Sessions 4–5), and Resolution (Session 6), with the midwife acting as teacher, counsellor, and surrogate throughout, involving the partner or family where appropriate (50, 51).

The intervention consists of six structured sessions, each with defined objectives and key activities, adaptable to the individual needs of the participant:

*Session 1*: Initial assessment and relationship building aims to establish contact, identify sources of anxiety and measure the baseline level of anxiety. In the introductory part, the midwife presents the purpose and principles of the intervention, ensuring confidentiality and an atmosphere of trust. Next, she conducts a diagnostic interview with open-ended questions regarding the patient’s fears, experiences and expectations, for example: “What are you most afraid of regarding childbirth?,” “Do you have previous childbirth experiences?,” “How do you remember them?,” “How does anxiety affect your daily functioning?.” At the end of the session, the midwife discusses and agrees upon the topics of subsequent sessions with the participant and provides educational materials, such as a programme leaflet and a notebook for recording thoughts and questions.

*Session 2*: Education on the course of childbirth is focused on increasing knowledge about the physiology of childbirth and verifying myths and misconceptions. The midwife discusses the stages—first, second and third—of childbirth in detail, explaining the symptoms, duration of each phase and standard medical procedures used at each stage (examinations, CTG monitoring, etc.). During the conversation, she addresses specific fears revealed earlier by the patient, providing comprehensive answers and correcting inaccurate information. In the case of multiparous women, a detailed interview is conducted regarding previous births, identifying difficult experiences and jointly seeking solutions and strategies with the midwife. The session is supported by materials such as brochures on the course of childbirth, anatomical diagrams and recommended educational videos.

*Session 3*: Methods of pain relief and stress management techniques is aimed at familiarising the patient with pharmacological and non-pharmacological methods of pain relief and teaching relaxation techniques. The midwife begins by explaining the physiology of labour pain and its role in the birthing process. She then presents non-pharmacological methods, such as breathing exercises, relaxation techniques, massages, labour positions, hydrotherapy or transcutaneous electrical nerve stimulation. Pharmacological methods are also discussed, including epidural anaesthesia, nitrous oxide and opioid medications, explaining their indications, benefits and potential limitations in detail. In the practical part, breathing and relaxation techniques are practised together with the patient; a companion may participate in the session at the patient’s request. At the end, the patient receives materials such as breathing exercise instructions, a list of pain relief methods and relaxation recordings. Partner participation will be documented in the session log and included as a covariate in sensitivity analyses if the frequency of attendance proves meaningful.

*Session 4*: Birth plan and communication with medical staff is focused on developing an individual birth plan and enhancing assertive communication skills with medical staff. The midwife introduces the concept of a birth plan as a document expressing the patient’s preferences and expectations regarding childbirth—for example, regarding labour positions, pain relief methods, the presence of a companion and skin-to-skin contact after birth. Together with the patient, she completes a birth plan form, discussing each option and providing objective information. The second part of the session is communication training—the midwife teaches the patient how to express her needs, ask questions and communicate assertively with the healthcare team. Specific phrases and conversation scenarios are practised, and the patient receives supporting materials, such as the completed birth plan, a leaflet on patient rights and a list of helpful questions for the staff.

*Session 5*: Anxiety management techniques and mental preparation for childbirth is aimed at equipping the patient with an individual set of psychological strategies for coping with anxiety before and during childbirth. The midwife begins by assessing the patient’s current emotional state and any progress made. She then deepens the discussion of relaxation and breathing techniques, introduces elements of mindfulness training, and works on the patient’s negative thoughts and beliefs—jointly developing positive affirmations and alternative, realistic thoughts. The next element is guiding a visualisation of a positive birth experience, aimed at desensitising anxiety and creating a constructive scenario in the patient’s imagination.

*Session 6*: Birth plan finalisation and Q&A concludes the intervention. The midwife summarises the entire process, reinforces the patient’s sense of competence and, if necessary, discusses options for further support. The patient receives a set of reinforcement materials. The PRAQ-R2 is administered at the last completed session to assess programme effectiveness, which may be Session 4, 5, or 6 depending on the number of sessions completed by the participant.

The intervention programme is flexible and can be adapted to the individual needs of the patient—both in terms of the number of sessions, topics, and format (with partner participation or independently). The intervention constitutes comprehensive educational support aimed at transitioning from anxiety to a sense of preparedness, control and inner peace ahead of the upcoming childbirth. An overview of the session structure, objectives and key activities is presented in Table 1.

**Table 1 tab1:** Intervention flow: objectives and activities per session.

Session	Objective	Key activities
1	Anxiety assessment and building rapport	Diagnostic interview, anxiety measurement (PRAQ-R2), session planning
2	Childbirth education	Discussion of labour stages, medical procedures, myth correction
3	Pain relief and stress management	Breathing and relaxation techniques, review of pain relief options
4	Birth plan and communication	Creating birth plan, assertive communication training with staff; final anxiety measurement (PRAQ-R2), if last session
5	Mental preparation and closure	Mindfulness, affirmations, positive visualisation; final anxiety measurement (PRAQ-R2), if last session
6	Birth plan finalisation and Q&A	Review of coping techniques, birth plan finalisation, Q&A, contact plan; final anxiety measurement (PRAQ-R2), if last session

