### Randomisation and blinding

2.11

Allocation to study groups at a 1:1 ratio will be performed using block randomisation with variable block sizes, computer-generated by a researcher not involved in recruitment. Allocation concealment will be ensured through sequentially numbered, opaque, sealed envelopes. The recruiting midwife will open the next consecutive envelope only after obtaining the participant’s final informed consent. Blinding of participants and intervention-delivering midwives is not feasible given the nature of the psychoeducational programme, consistent with standard practice in behavioural RCTs. Since all outcome questionnaires are self-completed via a secure online platform, no assessor is present at any data collection time point, which substantially mitigates assessment bias. The researcher responsible for data management and the data analyst will both be blinded to group allocation throughout the analysis phase, using coded group labels. Unblinding will only occur if authorised by the principal investigator for safety or ethical reasons and will be formally documented.

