### Data collection methods

2.12

All outcome measures will be collected via self-report questionnaires completed electronically by participants through the LimeSurvey platform at three time points: baseline (Time I, 24–30 weeks of gestation), post-intervention (Time II, 34–37 weeks of gestation), and postpartum (Time III, ≥6 weeks after delivery). No investigator-administered measurements will be performed. The data collection schedule is presented in Table 2.

To promote data quality, the LimeSurvey platform has been configured to prevent submission of incomplete questionnaires, to flag out-of-range responses, and to present items in a fixed order. All questionnaire links will be sent directly to participants via secure electronic communication. Data will be entered automatically into a password-protected database accessible only to the research team.

The following validated instruments will be used:

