### Statistical analysis plan

2.14

Analyses will be conducted according to randomised group allocation and will primarily follow the intention-to-treat principle, insofar as outcome data are available. The primary endpoint is PrA measured using the PRAQ-R2 at 34–37 weeks’ gestation. The primary analysis will compare post-intervention PRAQ-R2 scores between groups using analysis of covariance (ANCOVA), with treatment group as the main factor and baseline PRAQ-R2 score as a covariate. The primary outcome is assessed at two prenatal time points only: baseline and post-intervention. The postpartum assessment applies exclusively to secondary outcomes.

Secondary outcomes will be analysed using regression models appropriate to outcome type, with logistic regression for binary outcomes and linear regression for continuous outcomes. Secondary analyses will be considered supportive and exploratory; no formal adjustment for multiplicity is planned. Missing data will be described by study arm and time point. The primary analysis assumes data are missing at random (MAR); this assumption will be examined via sensitivity analysis, using a mixed-effects model for repeated measures applied to all available longitudinal data. Multiple imputation is not planned. The possibility of data missing not at random (MNAR) cannot be excluded and is acknowledged as a limitation. Stratification variables included in the randomisation will be entered as covariates in the primary ANCOVA model. A supportive per-protocol analysis will also be conducted among participants with observed primary endpoint data; in the intervention arm, this will additionally require completion of at least four intervention sessions. Two pre-specified sensitivity analyses will be conducted: (1) a linear mixed-effects model including midwife as a random effect, to account for potential clustering by intervention deliverer; and (2) a mixed-effects model for repeated measures applied to all available longitudinal data under a missing-at-random assumption, to assess the robustness of findings in the presence of incomplete data.

The mode of intervention delivery (in-person versus remote) will be recorded. As the trial is not powered for formal moderator analyses, any comparison by delivery mode will be considered exploratory and interpreted cautiously.

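### The intervention text adds PRAQ-R2 measurements inside midwife-led sessions, in one arm only, against a measurement plan that allows two online measurements in both arms

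*Protocol article*

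**What the plan says.** Two parts of the protocol article describe when and how the PRAQ-R2 is given.

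**Measurement plan.** Table 2 marks the PRAQ-R2 at Time I and Time II and leaves the 24–34 week intervention column empty for it. The Statistical analysis plan section restricts the primary outcome to these two measurements before birth. Collection is by self-report on LimeSurvey, and the Data collection methods section adds: "No investigator-administered measurements will be performed". The Randomisation and blinding section relies on this, saying that "no assessor is present at any data collection time point, which substantially mitigates assessment bias".

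**Intervention text.** Session 1 "aims to establish contact, identify sources of anxiety and measure the baseline level of anxiety", and Table 1 names the instrument in that session's activities: "Diagnostic interview, anxiety measurement (PRAQ-R2), session planning". For the end of the programme the text states: "The PRAQ-R2 is administered at the last completed session to assess programme effectiveness, which may be Session 4, 5, or 6". Table 1 repeats this for Sessions 4, 5 and 6 and calls it the final measurement. Only intervention women have sessions. They receive the same standard care and booklet as controls, "in addition to an individual psychoeducational programme led by a trained midwife".

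Nothing in the article says how the session scores relate to Time I and Time II, or that they are kept out of the analysis.

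**The concern.** The labels attached to the session scores are those of an outcome: baseline, final, a test of whether the programme works. One arm would therefore hold two values that could be called baseline and two that could be called post-intervention, while the other arm holds one of each.

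The outcome is self-reported by women who know their allocation. Completing the primary instrument two extra times, in sessions led by the person who teaches the coping skills, may change how it is answered at Time II, through familiarity with the items or a wish to show progress. Controls have no matching exposure. The Randomisation and blinding section offers the absence of an assessor as the main protection against this kind of bias, and the in-session administrations sit awkwardly beside it.

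There is also a data-handling risk. The sensitivity analysis is "a mixed-effects model for repeated measures applied to all available longitudinal data under a missing-at-random assumption". If session scores reached that dataset, they would enter with no control counterpart, and the extra records would show the analyst which coded group is the intervention.

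**Working it through.** No sample size, power or alpha figure bears on this point. The check is a count of administrations and a comparison of dates.

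**1. PRAQ-R2 completions before birth**

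- Control: Time I + Time II = 2.
- Intervention, read literally: Time I + Session 1 + last session + Time II = 4.
- Number stated in the Statistical analysis plan section: 2.

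**2. Can the Session 1 score be the Time I score?** No. Under Recruitment, the Time I PRAQ-R2 is completed online and decides eligibility. Under Randomisation and blinding, the envelope is opened only after final consent. Session 1 happens only in women already allocated to the intervention, so its score is post-randomisation. Table 2 does place a programme mark in the Time I column, but that does not alter this order.

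**3. Can the last-session score be the Time II score?** Inputs: sessions at 24–34 weeks, four to six sessions, one to two weeks apart, recruitment at 24–30 weeks, Time II at 34–37 weeks.

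Week of last session = week of first session + (number of sessions − 1) × spacing. Gap = Time II week − week of last session.

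| Start | Sessions | Spacing | Last session | Gap to Time II |
|---|---|---|---|---|
| 24 | 4 | 1 week | 24 + 3 × 1 = 27 | 34 − 27 = 7 to 37 − 27 = 10 weeks |
| 24 | 6 | 2 weeks | 24 + 5 × 2 = 34 | 34 − 34 = 0 to 37 − 34 = 3 weeks |
| 30 | 4 | 1 week | 30 + 3 × 1 = 33 | 34 − 33 = 1 to 37 − 33 = 4 weeks |

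The intervention and Time II windows touch only at week 34. Across these schedules the gap runs from 0 to 10 weeks. The first row is the early extreme: it needs a first session at exactly 24 weeks, the minimum number of sessions and the shortest standard spacing. A limitation in the Discussion says that the primary outcome is measured directly after the programme ends. That fits the last session better than a Time II up to 10 weeks later, and so adds to the uncertainty about which measurement is meant.

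**4. Is the in-session form incidental?** The Intervention fidelity section builds its checklist on the objectives and activities in Table 1 and sets acceptable adherence at 80% or more of required content per session. The in-session PRAQ-R2 is a listed activity in that table, so midwives following the protocol will collect it.

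**The case against.** The strongest reply is that the primary endpoint is not in doubt. The Primary outcome section, Table 2 and the Statistical analysis plan section all point to the 34–37 week score, with Time I as the covariate. This stands. A reader might infer that a session score could stand in for baseline or for Time II, but no sentence provides for that, and the restriction to two measurements before birth points the other way.

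The same restriction appears in the section that specifies the mixed model, so the natural reading of its longitudinal data is the scheduled data. This stands in part. It would be too strong to say that the model will take in the one-arm scores; the accurate statement is that the wording does not rule them out.

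It can also be said that the assurance about assessors refers to the three scheduled LimeSurvey time points, and that a form given in a session may still be completed by the woman herself. So it does not follow that the assurance is false for Time I and Time II. But the article does not present the session form as separate monitoring, and the labels it uses suggest otherwise.

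Finally, demand effects from individual sessions with a supportive midwife would exist without the extra forms, and the Discussion already acknowledges reporting bias. That is fair. Only the increment from repeated, in-session completion belongs to this point.

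**Conclusion.** The contradiction is real and should be resolved before sessions begin. The measurement plan allows two online PRAQ-R2 completions in each arm. The intervention text, followed as written, produces four in one arm and two in the other, with the extra two inside midwife-led sessions.

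The consequence is a risk of retest and demand effects in one arm only. Its size is unknown: the article contains nothing from which it could be estimated, and any point value set against the 3.27-point planning difference would be pure assumption. The primary ANCOVA is correctly defined and is not invalidated by the session scores. The exposed analysis is the repeated-measures sensitivity model, and only through wording that leaves the session scores neither in nor out. With a gap of 0 to 10 weeks under the stated session rules, the last-session score cannot be treated as equivalent to Time II.

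The count of four assumes that Table 1 is carried out literally, with Time I and Time II completed as well.

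**What to change.** - **Preferred:** remove the PRAQ-R2 from Session 1 and from the last session, in the Intervention section, in Table 1 and in the fidelity checklist derived from it. Give the midwife the Time I result for session planning, still not shown to the woman, in line with the Recruitment section.
- **If it is kept:** relabel it as non-outcome monitoring, drop the terms that present it as baseline, as final or as a measure of effectiveness, and acknowledge as a limitation that the arms differ in exposure to the primary instrument.
- **In either case:** state that only the pre-randomisation Time I and the 34–37 week Time II LimeSurvey scores enter the ANCOVA and the mixed model, identically in both arms, and make Tables 1 and 2 agree.

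The cost is a small edit to the protocol, session manual and checklist. Under the preferred option, midwives also lose an in-session progress score. Neither option changes the sample size, the visit schedule or the primary analysis.
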